### **8.2. Strengths and Limitations of the Clinical Investigation**

#### ***Strengths***

- Due to the different diagnoses treated at the Reha Zentrum Münster, no other medical facility is needed to recruit patients for this prospective comparative multiple case study.
- Great professional and scientific expertise of the study team
- Many different diagnoses can be investigated in a prospective comparative multiple case study.
- A case-oriented research strategy will be adopted to acquire knowledge about outcomes within the 8 disease groups, learn about similarities and differences between cases and neurological disorders within the individual intervention periods and emerging patterns, and for theory development (Ababacar et al., 2020; Nordbeck, 2013). However, the synthesis across cases will extend beyond the comparison of similarities and differences to generating information on the reasons and explanations as the findings from the RAGT intervention (Goodrick, 2014). In other words, except some degree of comparison that will be fundamental to the comparative multiple case study design, the differentiating feature of this study type is the emphasis on examining causality i.e., the extent to which the RAGT intervention caused the outcomes (Goodrick, 2014).
- In practice, this comparative multi case study will involve the analysis and synthesis of the similarities, differences and patterns across multiple cases, with the shared common goal of gaining knowledge about the feasibility, acceptability and preliminary effects of RAGT.
- Case selection will be performed using two different strategies: within disease groups, the 'Most Similar Systems Design' (MSSD) will be applied and between disease groups, the 'Most Different Systems Design' (MDSD) (Anckar, 2008; Przeworski & Teune, 1970) will be used, considering 8 neurological disease groups with symptom complexes involving distinct sensorimotor system parts of the central nervous system (upper and lower motor neurons including both the cerebrum and spinal cord, extra pyramidal motor system, peripheral nervous system, cerebellum and afferent pathways including their respective representations in the cortex). As for MSSD, it will mean to choose study patients that are similar in as many background characteristics as possible, but without systematically matching cases on all the relevant control variables. As for MDSD, the strategy will be to select patients that are as different as possible with respect to extraneous variables. The basic logic is that differences cannot explain similarities (Przeworski & Teune, 1970).
- The objectives, inclusion and exclusion criteria, endpoints and assessments and study procedures are clearly stated.
- Both a quantitative and qualitative data collection and analyses will be used.
- Mixing methods is a form of triangulation in research seen as mitigating the weaknesses found in single methods (Heale & Forbes, 2013). Triangulation in research is the use of more than one approach to researching a question. The

objective is to increase confidence in the findings through the confirmation of a proposition using two or more independent measures (Noble & Heale, 2019). The combination of findings from two or more rigorous approaches provides a more comprehensive picture of the results than either approach could do alone (Noble & Heale, 2019).

- The intervention of this study uses a standard RAGT protocol but is individualised and hence adapted to the different patient groups (Cases 1-8) and the individual performance level of the participants.
- Structured data documentation, management and evaluation will be used as outlined in this clinical investigation protocol
- Continuous monitoring for adverse events using a structured log and predefined evaluation criteria
- Comparative multiple case studies are useful for evaluating of feasibility, practicability, acceptability and preliminary results and for refining study procedures and therapy protocols before planning and commencing a large randomised controlled trial.

### ***Limitations***

- Low number of patients per diagnosis – due to low power, efficacy testing cannot be performed for the different disease groups but overall.
- Limited generalizability of results
- No control group
- No follow-up assessment

As outlined in Chapter 2.1, the purpose of this clinical investigation is to investigate the feasibility and acceptability and compare the preliminary effects of RAGT a mixed population with neurological diseases consisting of patients with stroke in the subacute and chronic phases and with severe and mild to moderate disability, MS, Parkinson's Disease, spastic para-or tetraplegia, mild to medium grade hereditary ataxia, acute or chronic inflammatory demyelinating polyneuropathy and motoneuron disease. A further purpose of this clinical investigation is to synthesise quantitative and qualitative results for examining causality i.e., the extent to which the RAGT intervention may have caused the outcomes.

The results from this study can be used for designing a full-scale randomised controlled trial. The study population and all study procedures have been specified a priori, the study team will strive to carry out all measures as planned and use a structured data documentation, management and evaluation as outlined in this clinical investigation protocol. The intervention of this study uses a standard RAGT protocol but is individualised and hence adapted to the different patient groups (Cases 1-8) and the individual performance level of the participants. Continuous monitoring for adverse events using a structured log and predefined evaluation criteria will be performed. Therefore, it is not expected that the limitations of this study negatively impact on the conduct of the clinical investigation, data quality and results.

## 9. SAFETY

### 9.2 Adverse event - definition

An adverse event (AE) is any unfavourable medical occurrence, unintended disease or injury or any unfavourable clinical sign that affects a patient during participation in this study and is not necessarily in a causal relationship with the study intervention. These may be diseases, signs and symptoms of disease that arise after the patient's inclusion in the study, or pre-existing diseases, signs and symptoms of disease that get worse after inclusion in the study. This excludes pre-existing diseases that do not get worse over the course of the study and adverse events that are associated with a concomitant medication. This definition includes events related to the study intervention and to the study procedures. According to the World Health Organization (2002), CIOMS (Council of International Organizations of Medical Sciences) and ICH (International Conference on Harmonisation), adverse events are medical occurrences temporally associated with the use of a medicinal product or intervention, but not necessarily causally related.

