**Adverse events**

Any adverse events and side effects will be systematically recorded and evaluated using a formal log including the type of adverse event, dates, severity, causality differentiated into serious/non-serious, actions to restore or improve the patient's wellbeing and outcome of the event. Study related adverse events such as training-related injuries will be treated and paid for. Severe adverse events will lead to early clinical investigation termination. ***This monitoring will be performed throughout the study.***

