#### **7.4 Concomitant treatment**

All study participants will receive their usual care including medical exams, rehabilitation assessments and goal setting, and medical treatment including medication. Study participants will undergo their usual inpatient rehabilitation comprising multidisciplinary rehabilitation (medical treatment, physiotherapy, occupational therapy, speech and language therapy, psychology counselling, dietetics etc.).

It is not planned to include patients who need relevant changes to their medication, but the medication will be adjusted and documented if the study PI considers this a requirement. Any changes or adjustments to medication that has an influence on the participant's walking ability/performance however will lead to the exclusion of the patient.

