### 9.3 Adverse reaction and side effect - definitions

A side effect (SE) is any adverse event defined above that has a causal connection with the study intervention. Side effects are often expected, and often refer to symptoms that are less harmful than adverse reactions. An adverse reaction is 'A response to a drug [or intervention] which is noxious and unintended, and which occurs at doses normally used in man for the prophylaxis, diagnosis, or therapy of disease, or for the modifications of physiological function' (WHO 1972).

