### 9.4 Serious incident - definition

A serious incident is any adverse event or any adverse reaction, which either

- Leads to death, or
- Is life-threatening, or
- Leads to lasting or serious disability or invalidity, or
- Makes inpatient treatment or an extension to inpatient treatment necessary (except for if the inpatient treatment was planned before participation in the study).

A distinction is made between a serious adverse event (SAE) or a serious adverse reaction (SAR), depending on whether it has a causal relationship with the study intervention.

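### The adverse-event definition in section 9.2 ignores cause, then excludes events linked to concomitant medication, so the AE count is biased downward and serious-event reporting is contradictory

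*Protocol*

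**What the plan says.** Section 9.2 opens with a cause-free definition: an adverse event is any unfavourable medical occurrence during participation, and it "is not necessarily in a causal relationship with the study intervention". The same paragraph then excludes two things: pre-existing disease that does not worsen, and "adverse events that are associated with a concomitant medication". The next sentence reads: "This definition includes events related to the study intervention and to the study procedures". The paragraph closes with the WHO, CIOMS and ICH position that "adverse events are medical occurrences temporally associated with the use of a medicinal product or intervention, but not necessarily causally related".

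Other sections build on this term:

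- Section 9.3: "A side effect (SE) is any adverse event defined above that has a causal connection with the study intervention". It then gives a separate, drug-style definition of an adverse reaction that does not carry the exclusion.
- Section 9.4: "A serious incident is any adverse event or any adverse reaction, which either" meets one of the listed seriousness criteria.
- Section 4.8, Adverse events: "Any adverse events and side effects will be systematically recorded and evaluated".
- Section 7.4: usual care continues for all participants, with "medical treatment including medication".

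**The concern.** Attribution to another cause normally follows recording. Here it acts as a filter before recording, and a vague one: an association is enough, and the exclusion applies to mild and serious events alike. In people with neurological disease on continuing medication, many symptoms could be linked to a drug by someone inclined to do so.

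The AE log is a named component of the primary feasibility endpoint (sections 2.2 and 4.8). Section 8.2 (Planned statistical analysis) reports the number of serious and non-serious events with it, and section 7.8 sends a safety summary to the sponsor. There is no control group whose count could show that events are missing. The study is also meant to inform a randomised trial, which would take over both the definition and the expected event frequency.

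**Working it through.** The protocol gives no AE rate or AE threshold, so there is no figure to reproduce. The check is to follow the term through the text for three kinds of event.

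**1. Event attributed only to a concomitant drug.**
- First sentence of 9.2: in, because cause is irrelevant.
- Exclusion in 9.2: out.
- Side effect (9.3): needs an adverse event as defined, with a causal link to the intervention, so out.
- AE log (9.7): records the events defined earlier in the chapter, so out.
- Counts in 8.2: taken from what is logged, so out.

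**2. Event linked to both a drug and the training.**
- Exclusion in 9.2: out.
- Next sentence of 9.2: in, because it is related to the intervention.
- Section 9.6: in, because a temporal relationship with the intervention is enough to make an event treatment-related.
- Result: both in and out, with no rule of precedence.

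**3. Serious event attributed to a drug.**
- Through the adverse-event branch of 9.4: out, inherited from 9.2.
- Through the adverse-reaction branch of 9.4: arguably in, because the definition borrowed in 9.3 speaks of a response to a drug.
- Last paragraph of 9.4: a serious adverse reaction is distinguished by its causal link to the study intervention, which points back to out.
- Section 9.8: the reporting sentence covers all serious events during the study, but its heading limits it to SAE/SAR.
- Result: contradictory.

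No section assigns the drug judgement. Section 9.7 has an authorised doctor assess association with the intervention, severity and seriousness, and does not mention medication. The two causality categories in 9.6 refer only to the study intervention.

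**Direction and size.** Let N be the events that meet the first sentence of 9.2, D those attributed only to a drug, and B those linked to both drug and training. The reported count is

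- N − D if the inclusion sentence prevails for B;
- N − D − B if the exclusion prevails.

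Since D and B cannot be negative, the count can only be too low, by between D and D + B. For serious events, D may be partly restored through the adverse-reaction route. The protocol gives none of N, D, B or the proportion of patients on medication, so the sign is known and the size is not.

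**The case against.** The strongest defence is that the text around the clause repairs much of the damage. A fall or blood-pressure drop during training is brought back in by the sentence after the exclusion and by the temporal rule in 9.6. A serious drug reaction can be argued into 9.8 through the adverse-reaction wording. One sentence of 9.7 requires all incidents and findings to go into the patient files and then the AE log. Falls in ambulatory patients have their own log (section 4.8), non-performed sessions are logged with reasons (5.2), and drop-out reasons (7.5) and medication adjustments (7.4) are documented.

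Most of this stands, and it limits what may be claimed. A reader might infer that:

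- **Medication-linked events leave no trace.** They do not disappear: patient files and the other logs may hold them. What is lost is the entry in the AE count.
- **Serious drug-associated events can never be reported.** The route is ambiguous, not closed.
- **Circulatory events in the device are the ones lost.** These are the events the text most clearly brings back in. Section 5.5 also excludes patients with uncontrolled orthostatic hypotension or other circulatory problems.
- **The feasibility verdict could change.** The three success criteria in section 4.8 are recruitment, retention and adherence, with no AE threshold.

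The defence does not repair the event attributed only to a drug. The broad sentence in 9.7 sits under a heading for adverse incidents (AE/AR) and follows a sentence limited to the events already defined, so at best it is one more conflicting statement. The other logs do not feed the AE counts.

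**Conclusion.** The defect stands. Section 9.2 contradicts its own first sentence, the international definition it cites, and the promise in section 4.8 to record any adverse event. Under the rule as written:

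- events attributed only to a concomitant drug are left out of the AE log and of the AE counts reported with the primary endpoint;
- events linked to both drug and training are classified both ways;
- the duty to report a serious drug-associated event is unclear.

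The AE count is biased downward by an amount the protocol does not allow to be quantified. Any percentage would be invented. The effect is on the safety component of the primary endpoint and the safety summary, not on a pass/fail criterion.

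This assumes that the site applies the exclusion as worded and that some participants are on medication. Section 7.4 supports the second assumption without quantifying it.

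**What to change.** Delete "adverse events that are associated with a concomitant medication", with the conjunction before it, from section 9.2. State that every event meeting the first sentence of the definition goes into the AE log. Record suspected attribution to concomitant medication as a separate causality item that may be marked together with treatment-related, and name who judges it. The CRF is not shown. If its AE log already has such an item, only the protocol text changes.

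Then reconcile 9.2, 9.3, 9.4, 9.6, 9.7 and 9.8, so that recording and serious-event reporting do not depend on whether a drug is suspected.

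The cost is one deleted clause, at most one extra log field and minor rewording. The downside is more AE entries and a less favourable AE count. The change belongs before recording starts, because events left out of the log cannot be reliably recovered later. It concerns recording only and leaves clinical management untouched.

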### 9.3 Adverse reaction and side effect - definitions

A side effect (SE) is any adverse event defined above that has a causal connection with the study intervention. Side effects are often expected, and often refer to symptoms that are less harmful than adverse reactions. An adverse reaction is 'A response to a drug [or intervention] which is noxious and unintended, and which occurs at doses normally used in man for the prophylaxis, diagnosis, or therapy of disease, or for the modifications of physiological function' (WHO 1972).

### 9.4 Serious incident - definition

A serious incident is any adverse event or any adverse reaction, which either

- Leads to death, or
- Is life-threatening, or
- Leads to lasting or serious disability or invalidity, or
- Makes inpatient treatment or an extension to inpatient treatment necessary (except for if the inpatient treatment was planned before participation in the study).

A distinction is made between a serious adverse event (SAE) or a serious adverse reaction (SAR), depending on whether it has a causal relationship with the study intervention.

### 9.5 Severity

The severity of incidents ((S)AE and (S)AR) are defined as follows:

- Mild – the intervention has to be interrupted due to the incident, but may be resumed on the same or the subsequent day. It is not necessary to consult a doctor for treatment in this case.
- Moderate – the intervention has to be interrupted due to the incident, but may be resumed on another day, but not immediately the subsequent day. It is not necessary to consult a doctor for treatment.
- Serious – the intervention must be stopped and cannot be continued due to the event (a drop-out according to Chapter 7.5)

## **9.6 Causality**

Causality is defined as follows:

- Treatment-related – It is either known that the adverse event may be caused by the study intervention or there is a justified suspicion that the study intervention caused the adverse incident or is there is a temporal relationship between the study intervention and the occurrence of the adverse incident.
- Not treatment-related – there is no justified suspicion that the study intervention caused the adverse incident or is there is no temporal relationship between the study intervention and the occurrence of the adverse incident.

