### 1.3 Risk-benefit analysis

The performance of the RAGT intervention and walking/balance tests may trigger adverse events and side effects. These may include increased and reversible fatigue and mild muscle pain associated with the gait training and will be minimised by using predefined and individualised strategies for progression of difficulty and breaks if needed, as outlined in detail in Chapter 7.2. The risk of this is therefore classified as low. RAGT is performed as part of the clinical routine in inpatient rehabilitation settings using different devices, with the LEXO® robotic gait trainer being a CE marked medical device that has undergone a comprehensive risk assessment (please see below for details). Any contraindications for the RAGT and any additional exclusion criteria related to this clinical investigation will be complied with. In addition, continuous monitoring for adverse events will be performed using a structured adverse events log. In addition, the clinical investigation site is an inpatient rehabilitation centre with a large medical team that is available on a 0-24/7 basis. At weeks 1 and 4, a semi-structured observation of the intervention will take part as a qualitative study measure, and any inconveniences of the participants will be noted and taken care of. So far, based on a systematic search within the worldwide most important databases for medical devices, no results and no adverse events were reported for the LEXO and its operating software tyroS. Furthermore, no adverse events happened with LEXO® from its market introduction. With respect to the walking, mobility and dynamic balance assessments, some of them are also performed as part of the clinical routine at the clinical investigation site and at other Austrian rehabilitation centres, with the remaining being carefully selected, standardised, validated assessments with excellent psychometric properties in patients with neurological diseases. As for the walking tests, it is assumed that falls may occur in rare cases, but these may also occur outside of the physiotherapy and study assessment setting in the daily lives of patients with neurological disabilities. To keep the risk of falls as low as possible, the walking assessment will be performed along a wall and under the supervision of a trained physiotherapist. Physical contact should not take place in order not to impact test performance but will be used to avoid a fall.

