## 7. STUDY PROCEDURES

### 7.1. Assessment and treatment schedule

The clinical investigation will comprise a screening, a baseline examination (T1), 16 intervention units over 4 weeks, and a post-intervention examination (T2).

The duration and number of the examinations (Table 1) will be used in addition to the patient's regular inpatient rehabilitation treatment. The intervention itself and some assessments will be performed as part of the clinical routine (for details, see Chapter 4). The PI, investigator and psychologists will perform any disease and cognition related examinations. All therapists conducting the movement-related assessments will be trained, and they will therefore work based on the same principles. Furthermore, the physiotherapists at the study site are using some the assessments on a daily basis (e.g., 10MWT, 6MWT), but for ensuring consistency, their training will be refreshed. The clinical investigation team (physiotherapists) that will conduct the RAGT intervention are trained on the use of the LEXO® device by authorised personnel from Tyromotion. In addition, the LEXO® is used also in the clinical routine at the Reha Zentrum Münster, which is why the physiotherapy team is familiar with the procedures. The clinical investigation team (physiotherapists) that will perform the motor assessments in this study will undergo training from [name] who is an experienced neurological physiotherapist and senior researcher to ensure consistency. In Table 8, the study procedures and schedule are presented; the table includes both the procedures which are performed ***within the clinical routine (highlighted green)*** and ***in addition to the clinical routine (highlighted yellow)***.

**Table 8:** Treatment and assessment regimen of a (screened, potential\*) study participant

| Procedure                                       | Dosage | Time                                                                            | Duration within clinical routine | Duration in addition to clinical routine |
|-------------------------------------------------|--------|---------------------------------------------------------------------------------|----------------------------------|------------------------------------------|
| Screening*                                      | 1x     | After checking for eligibility by the PI/investigator and the patient's consent | 10-15 min                        | --                                       |

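### Harm caused by the study's own added tests has no causality code: at baseline it falls to not treatment-related, and after the intervention it can fit either code

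*Protocol*

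**What the plan says.** The protocol recognises two sources of harm. Section 1.3 states: "The performance of the RAGT intervention and walking/balance tests may trigger adverse events and side effects". It also assumes that falls may occasionally happen in the walking tests. Section 9.2 says of adverse events: "This definition includes events related to the study intervention and to the study procedures".

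The classification steps that follow refer to one source only:

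- **9.3, side effect:** "A side effect (SE) is any adverse event defined above that has a causal connection with the study intervention".
- **9.4, SAE or SAR:** the split is made "depending on whether it has a causal relationship with the study intervention".
- **9.6, causality:** there are two codes. Treatment-related applies if the intervention is a known possible cause, or "there is a justified suspicion that the study intervention caused the adverse incident", or "there is a temporal relationship between the study intervention and the occurrence of the adverse incident". Not treatment-related applies if "there is no justified suspicion that the study intervention caused the adverse incident", or if there is no temporal relationship with the intervention.
- **9.7, assessment:** a doctor confirms the possible association with the intervention, the severity and the seriousness.

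On what is routine and what is added, 7.1 says: "The intervention itself and some assessments will be performed as part of the clinical routine". Table 8 puts all training time within routine care and lists 70-90 minutes in addition to routine for each of the baseline (T1) and post-intervention (T2) examinations. Table 7 marks the 10MWT and 6MWT as clinical routine, but not the FGA, TUG or FSST.

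**The concern.** The tests are named as a source of adverse events and side effects, but no later step lets an assessor record a test as the cause. Under 9.3 a test cannot cause a side effect at all, which contradicts 1.3.

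The structured adverse-event log is part of the primary endpoint, which is feasibility of the methods and of a full randomised trial. That trial could reuse the same tests. Its planners need to know whether harm came from the training, from the tests or from neither. The safety summary on the device that 7.8 requires for the sponsor needs the same separation. Section 12.4 also insures patients against damage from procedures as well as interventions, yet the causality field cannot identify damage of the first kind.

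**Working it through.** **1. How the two codes in 9.6 behave.** Take an injury caused by a study test, with no suspicion against RAGT.

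| When | Suspicion against RAGT | Temporal relationship with RAGT | Treatment-related met? | Not treatment-related met? |
|---|---|---|---|---|
| T1, before the first session | no | no | no | yes |
| T2, after four weeks of RAGT | no | can be argued | yes, through timing alone | yes, through absence of suspicion |

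Each code joins its conditions with *or*, so they are not mutually exclusive. An event with timing but no suspicion satisfies both. Neither code names the test. The T1 row relies on the order in the synopsis and Table 8, where the baseline examination comes before the intervention.

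**2. Consequence for the other labels.** If coded unrelated, the event is not a side effect and, if serious, is an SAE. If coded treatment-related at T2, it counts as a side effect of the intervention and, if serious, as an SAR. The error can therefore run in either direction: test harm hidden among unrelated events, or device harm overstated.

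**3. What the study adds to routine care (Table 8, minutes per patient).**

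- Training: 16 × 45 = 720 within routine, 0 added.
- Examinations: 2 × 70 = 140 to 2 × 90 = 180 added.
- Goal setting: 5 added.
- Total added: 140 + 5 = 145 to 180 + 5 = 185.
- Share from examinations: 140/145 = 96.6% to 180/185 = 97.3%.

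The 70-90 minutes include questionnaires and are not split by test in the protocol. From 4.8, the FGA takes 5-20 minutes, and the TUG and FSST under 5 each. Together these three take at most about 20 + 5 + 5 = 30 minutes of one examination, and only in ambulatory patients.

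**4. The plan's own figure.** The strata sum to 4 × 5 + 4 × 2 = 28, matching the stated sample size. Nothing in this point depends on it.

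**The case against.** A reader might infer that every test injury must be coded unrelated, that all such events across 28 × 2 = 56 examinations would be misclassified in that direction, and that a test battery causing falls would look safe. The documents do not support this:

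- At T2 the timing condition in 9.6 permits treatment-related, so the bias may go the other way. A T2 fall may also owe something to training, since 1.3 expects fatigue and mild muscle pain from it.
- The events are not lost. They count as adverse events under 9.2. Section 9.7 requires type, start and end, measures and outcome, so dates can be set against the examinations. Section 8.2 (planned statistical analysis) reports adverse events as well as side effects. Falls in ambulatory patients also have their own log.
- All serious incidents go to the PI and the ethics committee within the same time limit, whether SAE or SAR (9.8).
- The feasibility success criteria in 4.8 are recruitment, retention and adherence. None depends on a count of related events.
- The 97% is a share of added time, questionnaires included. It measures neither risk nor miscoding.
- Figure 6 (the assessment scheme) and the CRF are not shown and could hold a further category.

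All of this stands, and it limits the point. It does not remove it. The text of 9.3 to 9.7 gives no sign of a procedure category, and inferring cause from dates after the fact does not replace the assessor's judgement at the time.

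**Conclusion.** The point holds in a limited form. Sections 1.3 and 9.2 recognise harm from tests and procedures, but the visible classification rules provide no code for it. At T1 such harm falls to not treatment-related. At T2 it can fit either code and may be charged to the device. The result is misclassification, not loss of events, and it cannot change the outcome of the stated success criteria. What is lost is the ability to read test-related harm from the causality field in the adverse-event part of the primary endpoint.

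The number of events affected cannot be given; the protocol expects falls in the walking tests only rarely. The point is still relevant because RAGT is routine care, while the examinations account for nearly all the patient time the study adds.

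Three assumptions apply: Figure 6 and the CRF add no third category; T1 precedes the first RAGT session; and events at T1 and T2 are recorded, as the statement in 4.8 that monitoring runs throughout the study implies.

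**What to change.** - **9.6, and the assessment step in 9.7:** use three mutually exclusive codes: related to the study intervention, related to study procedures, related to neither. Define the last as the absence of both others, which removes the present overlap.
- **9.3 and 9.4:** keep side effect and SAR for the intervention. Widening them to test injuries would mix test harm into the device's counts and would sit badly with the definition of adverse reaction in 9.3. Flag serious procedure-related events separately in 9.4.
- **1.3 and 9.3:** align the wording, so that 1.3 does not expect side effects from tests that 9.3 excludes by definition.
- **8.2 (planned statistical analysis):** report intervention-related and procedure-related counts separately.
- **Figure 6, adverse-event log and serious-incident form:** check that they carry the same three codes.

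The cost is one extra tick box and a few sentences. The reported number of study-related events may rise slightly. Adding the code changes nothing in patient management.
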